### 3. SPONSOR

Pusan National University Hospital

### 4. FUNDER

Memorial Foundation for [name] by named Hyangseal, Korean Neurological  
Association (KNA-21-HS-08)

### 5. BACKGROUND AND RATIONALE

## 1) STUDY BACKGROUND

Benign paroxysmal positional vertigo (BPPV) is a disease characterized by short and repetitive rotational dizziness caused by head or posture transformation, and is one of the most common causes of dizziness. It is caused by the otoconia present in the utricle escaping into the semicircular canal due to degenerative changes in the inner ear or other causes. Migraine headaches, head injuries, other internal ear diseases, vestibular neuropathy, Meniere's disease, and stroke that invades cerebrovascular vessels such as the anterior inferior cerebellar artery (AICA) can also be important causes of secondary BPPV. Although the mechanism of separation from the utricle of the otoconia is unclear, it has been also reported to be related to autoimmune diseases, diabetes, and osteoporosis including accompanying inner ear disease and thyroid disease. The average incidence age is 50, and the incidence rate tends to increase as the age increases. It is known that the lifetime prevalence of BPPV is 2.4%, and the one-year incidence rate is about 0.6%.

[figure not shown]

**Figure 1. Mechanism of benign paroxysmal positional vertigo (BPPV). The detached otolith debris may be attached to the cupula (A: Cupulolithiasis) or free-floating in the semicircular canals (B: Canalolithiasis).**

The condition in which otoconia are adhered to the cupula is referred to as cupulolithiasis, while the condition in which they are suspended within the semicircular canal is known as canalolithiasis (Figure 1).

Cupulolithiasis of the posterior canal benign paroxysmal positional vertigo (PC-BPPV-cu) produces a positional nystagmus, with the upper pole of the eye beating torsionally towards the lower ear and vertically upwards, which lasts longer (> 1 min.) than experienced in canalolithiasis of PC-BPPV (PC-BPPV-ca) during Dix-Hallpike or half Dix-Hallpike maneuver (Figure 2). This diagnostic criterion helps distinguish PC-BPPV-cu from other forms of BPPV.

[figure not shown]

**Figure 2. Diagnostic maneuvers of cupulolithiasis type of posterior semicircular canal BPPV (PC-BPPV-cu). A. Dix-Hallpike maneuver B. Half Dix-Hallpike maneuver**

BPPV was traditionally considered as a benign condition that often resolved spontaneously over time without specific treatment. On average, PC-BPPV resolved about 39 days later. However, for the effective management of BPPV and to alleviate dizziness, accurate diagnosis and canalith repositioning maneuvers (CPM) are recommended.

Previous randomized controlled trials have proven that head-shaking and mastoid oscillation maneuvers effectively treat cupulolithiasis of the horizontal canal benign paroxysmal positional vertigo (HC-BPPV-cu). However, no data exist regarding the therapeutic efficacy of these maneuvers in PC-BPPV-cu.

## **2) STUDY PURPOSE**

The purpose of this study is to determine immediate and short-term therapeutic efficacies of head-shaking and mastoid oscillation maneuvers in PC-BPPV-cu.

## **6. PARTICIPANT ELIGIBILITY**

### **1) DISEASE**

: Posterior canal-Benign paroxysmal positional vertigo-cupulolithiasis (PC-BPPV-cu)

### **2) INCLUSION CRITERIA**

- A. A history of recurrent attacks of positional vertigo
- B. Positional nystagmus beating torsionally with the upper pole of the eye to the lower ear and vertically upward (to the forehead) and lasting > 1 min which was evoked by Dix-Hallpike or half Dix-Hallpike maneuver
- C. Absence of identifiable CNS disorders that could explain the positional vertigo and nystagmus.

### **3) EXCLUSION CRITERIA**

- A. Younger than 20 years
- B. Subjects with multicanal BPPV, cervical spinal problems, or cognitive dysfunction

- C. Subjects for whom, according to the investigators' opinions, participating in this clinical trial would pose a serious danger to their well-being or would result in unreliable outcomes at the end of the study.
- D. Subjects with severe, acute, chronic, progressive, or degenerative diseases that may affect this clinical trial.
- E. Subjects who do not agree to participate in this clinical trials.

#### **4) PARTICIPANT RECRUITMENT PLAN**

- A. All patients who meet the inclusion and exclusion criteria for this study among patients diagnosed with BPPV after visiting the study site during the study period will be included.
- B. The principal investigator of this study will not exclude patients who are likely to participate in this study based solely on race or socioeconomic status. Every effort will be made to ensure that as many patients as possible can participate in this study if the inclusion criteria are met, and the purpose of the study will be communicated to patients so that they can represent all patients with BPPV treated at the study site.

## **7. METHODS**

### **1) STUDY METHODS**

- A. Subjects with PC-BPPV-cu confirmed and treated at each clinic will be randomly assigned to the treatment groups or to the control (sham) group.

- B. A treatment maneuver was performed by a physician according to the assigned treatments or sham group.
- C. Treatment response was determined by the participating neurologists at each clinic without knowing the maneuver applied to each patient 30 minutes after the initial maneuver.
- D. If the patient had positional vertigo and nystagmus, the previously applied maneuver was repeated.
- E. The patients underwent re-examination 30 minutes later and were scheduled for follow-up the next day without additional treatment if they still presented with positional vertigo and nystagmus.

## **2) TREATMENT MANEUVERS**

The diagnosis and treatment (Canalith repositioning procedure) of participants who meet the inclusion/exclusion criteria are conducted from the baseline day (the first day) onwards. The choice of treatment is randomly assigned. Once the treatment method is selected, it is administered at each center accordingly.

- A. Head shaking maneuver: In a seated position with the head slightly tilted forward by approximately 30 degrees, shake the head from side to side at a frequency of 3Hz for 15 seconds
- B. Mastoid oscillation maneuver: Using a hand-held body massager (ID113, china), apply vibrational stimulation to the mastoid at a frequency of 100Hz. Each session of vibrational stimulation lasts for 1 minute, with a 1-minute rest period in between, and this cycle is repeated for a total of 3 times.
- C. Sham maneuver: Lie quickly in the opposite direction of the lesion and then rise again after 1minute.

[figure not shown]

**Figure 3. Sham maneuver**

### **3) RANDOMIZATION, BLINDING, AND CODE-BREAKING**

- A. Each study site will be assigned a unique four-digit center code when enrolled. Participants considered for entry to the study at their screening visit will be identified by a unique within-center serially assigned participant number. Participant numbers will be assigned automatically by the trial management system and no attempt will be made to allocate numbers outside the system.
- B. At their randomization visit (visit 0), participants who fulfill all the inclusion criteria and violate none of the exclusion criteria will be assigned a unique randomization number that will allow subsequent identification of their randomized treatment group allocation.
- C. The randomization will be done using a concealed, computer-generated list of management assignments based on the predetermined simple randomization schedule provided by REDCap© (ver. 9.5.2, Vanderbilt University, USA).
- D. The random allocation was designed in permuted blocks with a block size of 3.

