| Study methods                | 
 
1) Subjects with PC-BPPV-cu confirmed at each clinic will be randomly assigned (1:1:1) to the head shaking, mastoid oscillation, or control group using an interactive web response system.
 
2) A treatment maneuver will be performed once by a physician according to assigned treatments or sham group.
 
3) The treatment response will be determined by participating neurologists in each clinic without knowing the maneuver applied to each patient at 30 minutes after initial maneuver.
 
4) When the subjects will show positioning nystagmus, they will receive the previously applied maneuver again.
 
5) The subjects will undergo re-examination 30 minutes later and will be scheduled for follow-up the next day without additional treatment if they will still present with positional vertigo and nystagmus.
 
 |
| Target disease               | Posterior Canal-Benign Paroxysmal Positional Vertigo-Cupulolithiasis                                                                                                                                                                                                                                                                                                                                                                                                                                                                                                                                                                                                                                                                                                                                                                                                                                             |

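### Allocation is called both simple and blocked, and a fixed, published block of 3 for three arms makes assignments foreseeable to anyone who has seen the rest of the block

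*Protocol*

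**What the plan says.** Protocol section 7, part 3 (randomization, blinding and code-breaking), describes the allocation twice. Item C says it is "based on the predetermined simple randomization schedule provided by REDCap". Item D says "The random allocation was designed in permuted blocks with a block size of 3". Item C also calls the list concealed: "The randomization will be done using a concealed, computer-generated list of management assignments".

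The Study Summary gives three arms: subjects "will be randomly assigned (1:1:1) to the head shaking, mastoid oscillation, or control group using an interactive web response system". It plans 159 subjects, 53 per arm, in a multi-center trial.

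On who sees the treatment, section 7, part 1, item B says "A treatment maneuver was performed by a physician according to the assigned treatments or sham group". Section 7, part 2 describes three visibly different procedures: head shaking, a massager held to the mastoid ("Using a hand-held body massager (ID113, china), apply vibrational stimulation to the mastoid at a frequency of 100Hz"), and a sham in which the patient lies down on the side away from the lesion.

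On who may be left out, exclusion criterion C applies where "according to the investigators' opinions, participating in this clinical trial would pose a serious danger to their well-being or would result in unreliable outcomes".

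The protocol does not say whether blocks run within center or across centers, and it mentions no variation in block size.

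**The concern.** Two things look wrong.

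First, items C and D cannot both be true. Simple randomization draws each assignment independently, whereas permuted blocks restrict the draws. If *simple* was meant as unstratified, the text does not say so. A reader cannot tell which scheme was loaded into REDCap.

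Second, if item D is the real scheme, it is the most predictable blocked design that three equal arms allow, and its single block size is printed in a document that the sites hold. Hiding the list protects only against reading ahead in it. It does not protect against working out the next assignment from those already delivered, and the treating physician necessarily knows those. If the person who decides on enrolment also knows them, a foreseen assignment could influence whether a borderline patient is entered, and exclusion C leaves room for that judgement. The arms could then differ at baseline in ways that no later blinding repairs.

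**Working it through.** **Plan's own figure.** Section 8, part 2 uses two-sided α = 0.0167, power 80%, and rates of 70% and 38%. The mean rate is 0.54.

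n = [2.393·√(2·0.54·0.46) + 0.842·√(0.70·0.30 + 0.38·0.62)]² / 0.32² = (1.687 + 0.562)² / 0.1024 ≈ 49.4, so 50 per arm.

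With 5% dropout, 50/0.95 = 52.6, so 53 per arm and 159 in total. The stated figure reproduces and does not depend on the allocation method.

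**Which scheme fits equal arms.** In blocks of 3, 159/3 = 53 complete blocks on one list give exactly 53/53/53. Under simple randomization the probability of that split is 159!/(53!³·3¹⁵⁹) ≈ 0.5%. Equal arms may be only a target, so this favours item D without proving it.

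**Predictability when the whole block is seen.** Each block is one of 3! = 6 orderings of the arms. The chance of a correct guess is 1/3 at the first position, 1/2 at the second and 1 at the third.

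- Certain: 1/3, or 53 of 159.
- Guessed correctly: (1/3 + 1/2 + 1)/3 = 61.1%, or 53 × 11/6 ≈ 97 of 159.
- Under simple randomization: none certain, 33.3% guessed, or 53 of 159.

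For site staff this applies if blocks run within site, which is an assumption.

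**One central list over K equally recruiting sites (also an assumption).** The number of sites is not given in the text at hand. Staff who see only their own patients know an assignment for certain only when all three patients of a block fall at their site. That has probability 1/K², so the certain share is (1/3)(1/K²).

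For guesses, suppose staff even know their position in the block:

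- position 1: 1/3
- position 2: (1/K)(1/2) + (1 − 1/K)(1/3)
- position 3: (1/K²)(1) + 2(1/K)(1 − 1/K)(1/2) + (1 − 1/K)²(1/3)

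| List | Certain | Guessed correctly |
|---|---|---|
| Blocks within site | 33.3% | 61.1% |
| Central, K = 2 | 8.3% | (0.333 + 0.417 + 0.583)/3 = 44.4% |
| Central, K = 3 | 3.7% | (0.333 + 0.389 + 0.481)/3 = 40.1% |
| Central, K = 5 | 1.3% | (0.333 + 0.367 + 0.413)/3 = 37.1% |

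**Larger blocks, whole block seen and its size known.**

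- Size 6: certain (1 + 1/5)/6 = 20.0%; best guess 56.2% by simulation.
- Size 9: certain (1 + 1/4 + 1/28)/9 = 14.3%; best guess 53.2% by simulation.
- Equal numbers of blocks of 6 and 9: certain (1.200 + 1.286)/15 = 16.6%; best guess (6 × 56.2 + 9 × 53.2)/15 = 54.4%.

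The 16.6% is a ceiling. With sizes withheld, the end of a block is not known and fewer assignments can be certain.

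**The case against.** The strongest reply is that the predictability figure is conditional. A reader might infer that every third assignment is known in advance to staff. The documents do not support that as a fact. Section 7, part 3, item A makes participant numbers serial within center, but items B and C describe the randomization number and the list without mentioning center. On one central list the certain share at a site falls to a few percent. This part of the reply stands, and the size must be given as a range.

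Nor does the protocol say that the physician who delivers the maneuver also screens and enrols, or treats every patient at the site. The recruitment plan (section 6, part 4, item A) commits to including all eligible patients, and exclusion C is a general discretion clause whose scope has nothing to do with block size. This limits the claim to a possible bias. It does not remove it, because a commitment to include eligible patients does not bind a criterion that itself rests on opinion.

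A reader might also infer that the block size unblinds the outcome assessor. The documents do not support this. Section 7, parts 1 and 4 require an assessor who does not know the maneuver and is independent. To exploit the block, the assessor would already have to know earlier patients' maneuvers, and a physician who leaks could disclose the current maneuver under any block size. Resolution also requires absence of nystagmus, an examined sign, as well as absence of vertigo.

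Finally, the conflict between *simple* and blocks may be only loose wording, since item D is the more specific. That is likely, but the protocol still has to name one method.

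**Conclusion.** The point holds in two parts. The contradiction between items C and D rests on the text alone. The weakness of a fixed, published block of 3 follows from the three 1:1:1 arms: it is the smallest block possible, and the third assignment is determined by the first two.

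The practical size depends on list structure. It ranges from one third certain and 61% guessable (blocks within site) down to 1.3% certain and about 37% guessable (one central list over five equal sites), against 33% guessable by chance. Selection bias further requires that the person enrolling knows earlier assignments, which the protocol neither states nor rules out. Nothing in the document shows that bias has occurred, and the planned sample size is unaffected. This should be fixed because the remedy is cheap, but it does not invalidate the design.

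**What to change.** In section 7, part 3:

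1. Delete *simple* from item C, so that one method is named.
2. State in item D whether blocks run within center or on one list across centers.
3. Replace the fixed block of 3 with randomly varying larger multiples of 3 (for example 6 and 9). Keep the sizes out of the protocol, in a restricted document, and withhold them from sites.

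Possible wording: *Allocation is 1:1:1 by permuted blocks of randomly varying size, [within each center / on one list for all centers]; block sizes are documented separately and not disclosed to site staff.*

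If enrolment has begun, apply the new list to the remaining patients by amendment. If enrolment is complete, correct the text and report the scheme actually used. Parts of the protocol are in the past tense, so the stage cannot be told from the document.

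The cost before enrolment is a new allocation table in REDCap and a sentence or two; during enrolment it also includes the amendment and its approval. The gain is moderate for guessing (61% to about 54%) and larger for certainty (33% to at most about 17%). The downside is a slightly larger possible imbalance within small sites: within an unfinished block two arms can differ by up to 2 (size 6) or 3 (size 9), against 1 with size 3. A center-stratified comparison of resolution rates is optional.

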### **4) ASSESSMENTS**

- A. The absence of both vertigo and nystagmus was required to determine a resolution.

- B. Evaluation of treatment effect: The efficacy of treatment will be judged by an independent investigator blinded to the subject's information. If there is no improvement after the initial treatment, the patient will receive the same treatment once more. If there is still no improvement, the patient will visit the hospital again the following day for further evaluation.

## **5) TRIAL ENDPOINTS**

- A. Primary endpoint: The overall short-term resolution rate of positional vertigo and nystagmus in the following day.
- B. Secondary endpoint: The immediate efficacy of two trials of each maneuver within 30 minutes.

## **6) BENEFITS AND RISK FOR THE PARTICIPANTS**

- A. By participating in this study, it will be possible to save time and medical expenses by immediate treatments. Even when symptoms persist, subjects will be allowed to visit the hospital the next day and receive treatment, which is a faster process than using the general treatment system. Therefore, there are no anticipated risks from participation in this study.
- B. Subjects who visit the hospital due to persistent symptoms will receive a video-oculography test. The study team will be responsible for the medical fees of video-oculography.

## **7) DISCONTINUATION / WITHDRAWAL OF PARTICIPANTS**

- A. When subjects request discontinuation of the study
- B. In other cases where the study must be stopped at the discretion of the researcher

## 8. STATISTICS

### 1) DESCRIPTION OF STATICS METHODS

The demographic distribution of study participants by treatment maneuvers were compared using the Chi-squared test and one-way analyses of variance (ANOVA). If the results of the Chi-squared test were significant, additional post-hoc tests were performed using Bonferroni adjusted alpha level of 0.0167 per test (0.05/3). Statistical analyses were performed using SPSS (version 27.0; SPSS, Chicago, IL, USA).

The primary outcome was analyzed using both intention to-treat and per-protocol methods. Patients who did not complete the assessment in the following day were excluded from the per-protocol analysis.

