## ▪ STUDY SUMMARY

|                                                  |                                                                                                                                                           |
|--------------------------------------------------|-----------------------------------------------------------------------------------------------------------------------------------------------------------|
| Title                                            | Head Shaking and Mastoid Oscillation Maneuvers in Posterior Canal-Benign Paroxysmal Positional Vertigo-Cupulolithiasis (PC-BPPV-cu)                       |
| Supervision institution & Principal investigator | Department of Neurology, Pusan National University Hospital
[name] (Professor)                                                                |
| Funding agency                                   | Memorial Foundation for [name] by named Hyangseal, Korean Neurological Association (KNA-21-HS-08)                                                 |
| Study Purpose                                    | The purpose of this study is to determine immediate and short-term therapeutic efficacies of head-shaking and mastoid oscillation maneuvers in PC-BPPV-cu |
| Study design                                     | Multi-center, double blind, randomized controlled trial                                                                                                   |
| Study period                                     | IRB approval date ~ 4 years                                                                                                                               |
| Target population                                | Subjects with PC-BPPV-cu confirmed at the participating clinics during the study period.                                                                  |
| Number of subjects                               | 159 subjects (53 for each arm)                                                                                                                            |
| Vulnerable person                                | Not applicable                                                                                                                                            |

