| Safety evaluation    | Not applicable                                                                                                                                                                                                                                                                                                                                                    |
| Visit schedule       | Subjects will be scheduled to return to the clinic the next day if the vertigo and nystagmus will not resolve after two randomized maneuvers on the day of the visit.                                                                                                                                                                                             |
| Statistical analysis | Any difference in the treatment response would be determined using ANOVA and Chi-square test between the treatments and control groups.                                                                                                                                                                                                                           |
| Expected effects     | The head shaking and mastoid oscillation maneuvers would be recommended as initial treatment options for PC-BPPV-cu.                                                                                                                                                                                                                                              |

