### 2) THE NUMBER OF PARTICIPNATS

The following are assumed to calculate the sample size.

- A. Level of significance,  $\alpha=0.0167$
- B. The ratio of the treatment and control group = 1:1:1
- C. Power of the test,  $1-\beta = 80\%$
- D. In a previous study, we estimated that the proportions of patients with immediate resolution in PC-BPPV would 70% in the treatment groups, and 38% in the sham group.
- E. The formula for calculating the number of samples and the calculation results are as follows.
  - i.  $n1=n2=[Z_{\alpha/2} \sqrt{2\bar{P}(1-\bar{P})} + Z_{\beta}\sqrt{P_1(1-P_1)+P_2(1-P_2)}]^2 / (P_1-P_2)^2$
  - ii.  $n1$ = Sample size in the control group
  - iii.  $n2$ = Sample size in the treatment group

- iv.  $p_1, p_2$  = Expected outcome rates for each group
- G. Based on these estimations, a sample size of 159 participants is obtained with a dropout rate of 5%.
- H. The calculated sample size considers the drop rate, and in actual clinical research, more or fewer participants may be required than the calculated number of study subjects. When 30%, 60%, or 90% of the expected study subjects are achieved, a Data and Safety Monitoring Board meeting will be held to determine whether the number of participants is appropriate.

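### The protocol does not say which threshold decides the primary comparisons (0.05 or 0.0167), and with three arms the Bonferroni step after a significant global test is redundant

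*Protocol*

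**What the plan says.** Four places in the protocol bear on how the arms are compared.

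- **Section 8.1 (statistical methods).** "The demographic distribution of study participants by treatment maneuvers were compared using the Chi-squared test and one-way analyses of variance (ANOVA"). The next sentence makes further testing conditional on a significant chi-square: "additional post-hoc tests were performed using Bonferroni adjusted alpha level of 0.0167 per test (0.05/3"). For the primary outcome the section gives only the analysis sets, intention-to-treat and per-protocol.
- **Study Summary, statistical analysis row.** "Any difference in the treatment response would be determined using ANOVA and Chi-square test between the treatments and control groups". It gives no multiplicity rule. Section 7.4 makes the response binary, because resolution requires that both vertigo and nystagmus be absent.
- **Section 8.2 (sample size).** The item headed "Level of significance" is set at 0.0167, with 80% power and a two-group formula that uses Z at α/2. The assumed rates are given as "would 70% in the treatment groups, and 38% in the sham group", and the allocation is 1:1:1. The result is 159 in total after 5% dropout, which the Study Summary gives as "159 subjects (53 for each arm").
- **Section 8.3 (level of significance).** A single entry, P < 0.05, with no test, endpoint or family of comparisons named.

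**The concern.** Read literally, the post-hoc rule governs baseline tables, and the treatment comparison has two candidate tests and no stated pairwise threshold. ANOVA is not the natural test for a yes/no outcome, and naming two tests for one outcome leaves a choice open. A pairwise p-value between 0.0167 and 0.05 would be a success under one reading and a failure under another, and the document does not settle which.

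A second question arises if the 0.0167 rule is meant for the outcome. The rule is then a global three-group test followed by Bonferroni. With exactly three arms the second correction is not needed to hold the family-wise error, so the trial would use a stricter rule than it needs. This matters because the protocol hopes to recommend both maneuvers.

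**Working it through.** **Inputs.** From Section 8.2: resolution rates 0.70 (each maneuver) and 0.38 (sham), α = 0.0167 two-sided, power 80%, allocation 1:1:1, dropout 5%. From the Study Summary: 53 per arm. The 0.0167 is 0.05/3, as Section 8.1 writes it.

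**1. Reproduce 159.** The protocol's formula is n = [Z(α/2)·√(2P̄(1−P̄)) + Z(β)·√(P1(1−P1)+P2(1−P2))]² / (P1−P2)².

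- P̄ = (0.70 + 0.38)/2 = 0.54, and √(2 × 0.54 × 0.46) = 0.7048.
- √(0.70 × 0.30 + 0.38 × 0.62) = √0.4456 = 0.6675.
- At 0.0167: Z = 2.393 and Z(β) = 0.842, so n = (1.687 + 0.562)²/0.32² = 5.057/0.1024 = 49.4, rounded up to 50. With dropout, 50/0.95 = 52.6, rounded up to 53, and 3 × 53 = **159**. This matches.
- At 0.05: Z = 1.960, so n = (1.381 + 0.562)²/0.1024 = 36.9, rounded up to 37. With dropout, 37/0.95 = 38.9, rounded up to 39, and 3 × 39 = **117**.

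The sizing therefore assumes two-sided pairwise outcome tests at 0.0167.

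**2. Why Bonferroni is redundant after the global test.** Three arms give three pairwise null hypotheses. If any two of them are true, all three rates are equal, so the only intersection hypothesis is the global null. A closed test rejects a pair when the global test and that pair's own test are each significant at 0.05. If all rates are equal, a false claim requires the global test to reject (5%). If exactly one pair is equal, only that pair can be falsely rejected, at its own 5%.

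**3. Operating characteristics.** Independent binomial arms, uncorrected Pearson chi-square, all outcomes enumerated.

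| Rule | Any false claim, all arms 38%, n = 53 | Power per sham comparison, 70/70/38%, n = 53 | Power for both maneuvers, n = 53 | Per comparison / both, n = 50 |
|---|---|---|---|---|
| Global 0.05, then pairs at 0.0167 | 4.2% | 82.4% | 72.1% | 82.9% / 73.2% |
| Global 0.05, then pairs at 0.05 (closed) | 5.0% | 89.9% | 85.1% | 89.5% / 85.3% |
| Pairs at 0.05, no global test | 9.7% (two sham comparisons), 13.0% (three pairs) | 91.4% | 85.3% | 91.5% / 85.6% |

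- The gain from the closed test at 53 per arm is 89.9 − 82.4 = 7.5 points per sham comparison and 85.1 − 72.1 = 13.0 points for both.
- Nearly all the loss comes from the Bonferroni step. Without the global gate, 0.0167 gives 82.4% at n = 53 and 83.0% at n = 50, so the gate costs about 0.1 point at most under these rates.
- The chi-square is approximate at these sizes. Under the closed rule the all-null error is 5.2% at n = 50. With rates 70/38/38% the one true null pair is rejected in 5.3% at n = 53, as it is (5.3%) without the gate.
- If one maneuver is intermediate (70/54/38%, n = 53, simulated), the closed rule moves power against sham from 82.4% to 85.5% for the stronger maneuver and from 21.8% to 36.1% for the weaker.

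**The case against.** The passages can be read together without conflict. The Study Summary names chi-square for response, Section 8.1 follows a significant chi-square with 0.0167 per test written as 0.05/3, Section 8.2 sizes at 0.0167, and 0.05 is then the overall level. The exact match at 159 supports this reading. It stands as the likely intent, and on it the alpha statements do not contradict each other.

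A reader might infer that the protocol roughly doubles its false-positive risk. The documents do not support that. The 9.7% and 13.0% figures need ungated pairwise tests at 0.05, which no passage prescribes. The Study Summary sentence can equally mean one three-group chi-square, whose error at 53 per arm is 5.0%.

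A reader might also infer that the trial is underpowered or loses power it was sized to have. It does not. The 159 was computed at 0.0167, and the 80% target is met at that level. The protocol sets no power target for succeeding on both maneuvers. Nor can the two worries hold together: if the 0.0167 rule covers only demographics, it costs no power on the outcome; if it covers the outcome, error is controlled.

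Finally, test detail is often left to an SAP, which is not shown. That would excuse silence. Here, however, the protocol does state tests and levels: it attaches the rule to demographics, names ANOVA for a binary response, and leaves 0.05 unexplained.

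**Conclusion.** The point holds as an ambiguity in the deciding threshold and as an avoidable inefficiency. It is not a demonstrated inflation of type I error, and the sample size is not wrong.

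On the likely reading, family-wise error is about 4 to 5% and power per sham comparison is 82 to 83%, above the stated 80%. Family-wise error would reach about 10% (two sham comparisons) or 13% (three pairs) only if someone took 0.05 as an ungated pairwise level. Replacing Bonferroni by the closed test is worth about 7 points per sham comparison and 12 to 13 points for both maneuvers, with no added participants.

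These figures assume independent arms, the uncorrected Pearson test, 50 to 53 analysed per arm, and the protocol's own rates of 70% and 38%. Section 8.2 describes those as immediate resolution rates, whereas the primary endpoint is next-day resolution; they are taken here as given.

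**What to change.** - **Section 8.1.** Name the primary endpoint. Compare the three arms by one Pearson chi-square at 0.05 and, only if it is significant, test each pair by chi-square at 0.05, stating that this is a closed test. Keep ANOVA for continuous baseline variables.
- **Study Summary.** Remove ANOVA from the treatment-response sentence.
- **Section 8.3.** Say that 0.05 is the level of the global test and of the closed pairwise tests.
- **Section 8.2.** Keep 159. Add that it was derived conservatively at 0.0167, so power per comparison exceeds 80% under the closed test, and that the same formula at 0.05 would give 117. Without this note the sizing and the decision rule would no longer agree.

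If the sponsor prefers Bonferroni, that is valid and already matches 159. Sections 8.1 and 8.3 should then state that 0.0167, not 0.05, decides each pairwise claim on the primary endpoint.

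The cost is wording only. The rule should be fixed before unblinding.
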